### Maternal anthropometry

If the mother is available, her weight and height will be measured at baseline (or when available) using electronic scales and an adult height board according to the SOP. Maternal anthropometrics have been associated with the growth of their offspring and it is therefore of interest to measure maternal BMI in this study [30].

## House mapping and WASH assessment

At the first participant home visit study staff record the GPS coordinates of the home site location, in case home follow-up is needed at a later stage. Study staff also make a short assessment of WASH characteristics including; water source, basic sanitation and use of soap. More information is provided in the SOP.

## Nutrition assessment

General nutrition intake is assessed at baseline using an adapted food frequency questionnaire. The food frequency questionnaire gives an indication of breastfeeding status and diet.

## Bioimpedance

Fat mass and fat-free mass are measured using bioimpedance, at baseline and 12 weeks. Bioimpedance is taken while the child is lying down, preferably after 10 minutes rest. Once the reading begins, it takes less than 10 seconds to complete. A maximum of three repeated measurements are taken and all measurements are carried out by trained staff in accordance with the SOP. Electrode stickers are placed at the dorsal surface of the hand and foot. Impedance is measured through the right side of the body where possible (stickers placed on the right side). The current passed is not harmful and cannot be felt. The equipment is approved for medical use according to European standards.

## Child development

The Malawi Developmental Assessment Tool (MDAT) is a culturally relevant, reliable and sensitive child developmental assessment tool for use in African settings (Gladstone et al., 2010). The MDAT has been adapted and validated for use in Uganda. Child development index (CDI) is calculated at baseline and 12 weeks using a version of the MDAT that is both in English and translated to Lusoga. A study staff member trained in child development assessment will assess according to the SOP. The tool focuses on four domains; gross motor, fine motor, language and social development. An overall score for each domain is given according to the number of items passed.

## Phone call follow-up

When appointments are made, either at recruitment, inclusion or follow-up, caregivers are asked for phone contact information in order to follow-up on the appointment attendance. If included, selected study staff will attempt to establish phone contact to enquire about recent medical history, milk consumption and to monitor stool sample collection, LNS-LQ compliance or the resolution/worsening of adverse events where applicable.

## Sample collection and storage

### Stool

Stool samples are collected for later analysis of markers of gut function and microbiota, see table 2 for an overview of stool sample collection. Approximately 5-10g is collected from the study participant at two time-points; at baseline and at 12 weeks. Caregivers are given a sample collection kit and instruction on how and when to collect and return samples. Samples may be collected during the respective clinic visit if available. The sample may be stored at room temperature for up to 5 days after collection. Further details concerning sample collection are provided in the SOP. Stool samples are stored at −20 °C until delivery to the main storage site in Kampala where samples are then stored at −80 °C until they can be shipped internationally for analysis. See figure 5 for an overview of stool sample cold chain process.

**
[figure not shown]
**

**Figure 5**: Stool sample flow, including approximate time frames and approximate temperatures

### Blood

Blood samples are collected and stored for later measurement of selected growth factors, nutrient status, markers of gut function and markers of inflammation (table 2). Samples are collected by trained study nurses at baseline and at 12 weeks. A total of 6.0 ml of venous blood is collected by standard phlebotomy.

A drop of blood will be used to measure HIV status (preferably at baseline). Caregivers will be referred to the government health clinic for HIV counselling services where applicable. Whole blood haemoglobin status will be measured using a Hemocue at baseline and at 12 weeks. Additionally, all participating children will be tested for malaria at baseline using a RDT test. Further details concerning sample collection are provided in the SOP.

[figure not shown]

**Figure 6**: Blood sample flow, including approximate time frames and approximate temperatures

### Transportation and shipment of samples

Once a week or as frequently as possible, blood and stool samples are transported from the laboratory in Jinja to a secure storage facility in Kampala where they are stored at -80⁰C until they can be shipped internationally for later analysis. Prior to shipment of samples, a materials transfer agreement (MTA) will be established. Samples are collected in storage and shipped in larger shipments. All samples are kept at -80°C until shipment, and are stored at -80°C while they are awaiting analysis in Denmark. Samples are stored until minimum 5 years after study termination.

### Sample collection and analysis plan

| **Table 2: Sample collection and analysis plan** | | | | | |
| --- | --- | --- | --- | --- | --- |
| Collection | | | | Analysis | |
| Sample  Collected | Test | When to collect | Type of sample | Suggested method of analysis | Site of analysis |
| Blood sample, 6 ml | HIV status | Baseline | Whole blood, drop | RDT Antibody (all ages) + PCR (only <18 months (if available)) | Uganda – clinic |
|  | Malaria | Baseline | Whole blood, drop | RDT – smear |  |
|  | Hb, | Baseline and  week 12 | Whole blood, drop | Hemocue RDT |  |
|  | IGF-1, insulin |  | Serum/plasma | ELISA | Shipment abroad after study completion |
|  | CRP, AGP |  | Serum | ELISA |  |
|  | Iron status (SF, sTfR), vit A |  | Serum | ELISA |  |
|  | Citrulline |  | Plasma/serum | LC/MS/MS |  |
|  | Folate and vitamin B-12 |  | Plasma | ELISA |  |
|  |  |  |  | ELISA |  |
| Stool sample, approx.1-5 g | MPO | Baseline and  week 12 | Fecal sample supernatant, 1.0g | ELISA | Shipment abroad after study completion |
|  | NEO |  | Fecal sample supernatant , 1.0g | ELISA |  |
|  | AAT |  | Fecal sample supernatant , 1.0g | ELISA |  |
|  | Gut microbiota |  | Fecal sample supernantant , 1.0g | HTS-DNA PCR |  |

RDT: Rapid diagnostic test; PCR: Polymerase chain reaction; ELISA: Enzyme-linked immunosorbent assay; LC/MS/MS: Liquid chromatography tandom mass spectrometry; Hb: Haemoglobin;; IGF-1: Insulin Growth Factor-1; CRP: C-reactive protein; AGP: Alpha-1-acid-glycoprotein; SF: Serum ferritin; sTfR: Soluble transferrin receptors; MPO: Myeloperoxidase, NEO: Neopterin; AAT: Alpha-1-antitrypsin; HTS-DNA: High throughput DNA sequencing

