| **Measurable Outcomes:**  Primary outcome: Knee-heel length (mm) and total length (cm) over 12 weeks.  Secondary outcomes: HAZ, WAZ, WHZ, weight gain (g), body composition (bioimpedance and skin folds), head circumference, MUAC, haemoglobin (Hb) and child development, based on the Malawi Developmental Assessment Tool (MDAT) over 12 weeks.  Tertiary outcomes: Growth factors [Insulin-like growth factor-1 (IGF-1), insulin], markers of nutrient status [ferritin, soluble transferrin receptor (sTfR), vitamin B12, vitamin A and folate], markers of systemic inflammation, intestinal inflammation and intestinal function [C-reactive protein (CRP), alpha-1-acid glycoprotein (AGP), myeloperoxidase (MPO), neopterin (NEO), alpha-1-antitrypsin (AAT), citrulline], gut microbiota (diversity and composition), and morbidity over 12 weeks. | |
| **Study participants:**  750 children aged 12 -59 months with a HAZ <-2. | |
| **Study design:**  A randomised, double-blinded, community trial, testing four different large-quantity lipid-based nutrient supplements (LNS-LQ) in a two-by-two factorial design. A fifth un-supplemented group is included as a reference. Shown in figure 1. | |
| \|  \|  \| + Milk protein isolate (MPI) \|  \| + Soy protein Isolate (SPI) \| \| --- \| --- \| --- \| --- \| --- \| \| Whey permeate  (+ WP) \| A. \| LNS-LQ + MPI + WP  n=150 \| C. \| LNS-LQ + SPI + WP  n=150 \| \| No whey permeate  (-WP) \| B. \| LNS-LQ + MPI – WP  n=150 \| D. \| LNS-LQ + SPI - WP  n=150 \|  \|  \| Family diet \| \| --- \| --- \| \| E. \| Reference n=150 \|   **Figure 1:** Four large-quantity lipid-based nutrient supplements (LNS-LQ) in a two-by-two factorial design. Reference group continues with family diet. n= number of children allocated. MPI: Milk protein isolate, WP: whey permeate, SPI: soy protein isolate | |
| **Study site and recruitment:**  Study clinics are run from selected community health centres. Recruitment will take place in villages located nearby these selected community health centers | |
| **Participant inclusion:**  If both inclusion and exclusion criteria are fulfilled and informed consent is given, children are randomly allocated to one of four LNS-LQ or to an un-supplemented group. | |

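### The stool specification gives two collection amounts that meet only at 5 g, lists supernatant as the material for microbiota sequencing, and leaves time to freezing unrecorded (tertiary outcomes only)

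*Protocol*

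**What the plan says.** Two places in the Protocol's section on data collection and measurements specify the stool sample.

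- **Stool (running text).** The purpose is stated as "Stool samples are collected for later analysis of markers of gut function and microbiota". On amount: "Approximately 5-10g is collected from the study participant at two time-points; at baseline and at 12 weeks". On storage: "The sample may be stored at room temperature for up to 5 days after collection". Samples may be produced at the clinic visit or collected at home with a kit. They are then held at −20 °C and later at −80 °C until shipment. For the rest, "Further details concerning sample collection are provided in the SOP".
- **Table 2, Sample collection and analysis plan.** The sample is entered as "Stool sample, approx.1-5 g". Four tests follow: myeloperoxidase, neopterin, alpha-1-antitrypsin and gut microbiota. The myeloperoxidase row reads "Fecal sample supernatant, 1.0g | ELISA", and the other two ELISA rows name the same material and amount. The microbiota row reads "Fecal sample supernantant , 1.0g | HTS-DNA PCR".

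The protocol summary gives the outcome these samples must support as "gut microbiota (diversity and composition), and morbidity over 12 weeks", among the tertiary outcomes. The three stool inflammation markers are tertiary as well.

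**The concern.** Three features of the specification do not fit together.

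1. **Amount.** Staff who follow the running text and staff who follow Table 2 aim at different quantities, and the lower end of Table 2 lies below the sum of its own rows. No order of priority is given for a short sample.
2. **Material.** Table 2 sends supernatant to DNA sequencing. A supernatant is the liquid left once solids, cells included, have been spun down. An outcome defined as the diversity and composition of the bacterial community should not be read from a fraction depleted of that community.
3. **Time to freezing.** Up to 5 days at room temperature is allowed, and the place of collection varies. The delay before freezing can therefore differ between children, and the protocol mentions no recording of it.

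At stake are four tertiary outcomes, one of which bears on the prebiotic effect of lactose that the Background offers as part of the case for whey permeate. Stool is taken only twice per child, at baseline and week 12, so a short or poorly handled sample cannot be replaced later.

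**Working it through.** **Inputs**

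- Stool section: 5 to 10 g, approximate.
- Table 2, sample column: 1 to 5 g, approximate.
- Table 2, stool rows: four tests at 1.0 g each. I read this as grams of stool; the table does not say so outright.
- Planned samples: 750 children × 2 time points = 1,500.

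The Protocol states no total requirement, so there is no figure of its own to reproduce.

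**Step 1: do the two amounts agree?** Overlap runs from the larger lower bound to the smaller upper bound: max(1, 5) = 5 g to min(5, 10) = 5 g. The ranges share the single value 5 g.

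**Step 2: what do Table 2's rows require?** This depends on whether portions are shared, which is not stated. Three readings cover the range:

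- separate portions: 4 × 1.0 = 4.0 g
- one ELISA portion plus one microbiota portion: 1.0 + 1.0 = 2.0 g
- one portion for all four: 1.0 g

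**Step 3: amount collected minus amount required**

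| Reading | Required | Table 2 low (1 g) | Table 2 high (5 g) | Text low (5 g) | Text high (10 g) |
| --- | --- | --- | --- | --- | --- |
| Separate portions | 4.0 g | −3.0 | +1.0 | +1.0 | +6.0 |
| ELISAs share one | 2.0 g | −1.0 | +3.0 | +3.0 | +8.0 |
| All share one | 1.0 g | 0.0 | +4.0 | +4.0 | +9.0 |

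The running text covers every reading. Table 2's lower end covers only the last.

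**Step 4: how amount and material interact.** The reading under which 1 g suffices has the sequencing drawn from the same supernatant portion as the ELISAs. If microbiota is moved to whole stool at the listed 1.0 g, that reading falls away. The smallest requirement is then 2.0 g, and Table 2's lower end is short by at least 1.0 g.

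**Step 5: which column carries the material?** Table 2 puts the material and amount under the type of sample, within the collection half of the table. The neighbouring entries in that column distinguish whole blood, serum and plasma. The heading that marks the analysis as merely suggested belongs to the next column, which holds ELISA and sequencing. The supernatant entry is therefore a sample specification. It matches the three rows above it apart from a spelling slip, which suggests that it was repeated from them.

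**Step 6: storage.** A clinic sample could be frozen soon after collection, while a home sample may wait up to 5 days. The documents give no figure for the effect of that delay on any assay, so none is calculated.

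**The case against.** A reader might infer that the stool plan cannot deliver its four assays. The documents do not support that. The running text's 5-10 g covers even the largest requirement of 4.0 g, and so does the upper end of Table 2. The 4.0 g is itself an inference, because the Protocol never says that the portions are separate. Both amounts are approximate, and Table 2 sets no acceptance minimum.

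Nor is the wrong material locked in. The text describes stool being frozen and shipped, with no centrifugation before freezing, and the analysis follows study completion. A laboratory could still extract DNA from stored stool. How the supernatant would be prepared is not described.

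A second tempting inference is that variable storage would swamp or imitate a treatment effect. This too goes beyond the documents. The kit, the SOP and the stool-flow figure, whose caption promises time frames and temperatures, are not shown, so a preservative cannot be ruled out. The four supplement arms are blinded, the baseline kit is handed out before caregivers learn the allocation, and all arms attend at week 12. Under randomisation, uneven delay would mainly add noise.

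These objections remove the strong readings. They leave standing the disagreement in amount, the lower end of Table 2, the supernatant entry and the unrecorded delay.

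**Conclusion.** The concern holds as an inconsistent and partly wrong specification that affects tertiary outcomes only. The primary and secondary outcomes and the sample size are untouched.

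- **Certain from the text:** the two collection ranges meet only at 5 g, and Table 2 names supernatant for microbiota sequencing.
- **Conditional on portion sharing:** at its lower end Table 2 falls short of its own rows by 3.0 g with separate portions or 1.0 g if the ELISAs share one. There is no shortfall only if all four assays use one portion.
- **Resting on the ordinary meaning of supernatant:** the listed material is depleted of the bacteria to be profiled.
- **Possible but unquantified:** time to freezing may range up to 5 days and add noise. Whether it matters depends on a kit and procedures that are not shown.

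The correction is worth making because it is cheap and up to 1,500 samples are collected under this specification.

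**What to change.** 1. State one collection amount, the same in the Stool section and in Table 2, large enough for all four assays. Say whether the 1.0 g portions are shared. If they are not, the amount must cover 4.0 g.
2. Change the microbiota row of Table 2 to whole stool, aliquoted before any dilution or centrifugation, and bring the stool SOP into line.
3. Record the time of collection and the time of freezing on the CRF, and examine time to freezing in a sensitivity analysis of the stool outcomes. State in the Stool section whether the kit contains a preservative.

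The cost is wording in two places and the SOP, two CRF fields and a little more analysis. I would not add a same-day return or a fixed cut-off in hours. No figure in the Protocol supports a particular limit, and a baseline home sample would need an extra trip or staff collection, because the next scheduled clinic visit is at week 2.

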## Deterioration and loss to follow-up

*Proportion deteriorated to MAM or SAM* is the proportion of children who have deteriorated according to their status at inclusion. Either to MAM, measured as MUAC < 125 mm and ≥115mm or WHZ between -3 and -2, OR the proportion of children who have deteriorated to SAM, measured as WHZ <-3, MUAC <115mm or the presence of nutritional oedema.

*Proportion and qualification of morbidity* is the number of episodes, number of days with and the qualification of morbidity, during the 12 week intervention period. During the baseline clinical examination, signs and symptoms of the following are assessed: pneumonia (moderate or severe), diarrhea [acute watery (<14 days), acute bloody (<14 days), persistent (≥14 days)], fever (>38⁰C), common cold and other. The caregiver is given an exercise book at inclusion to be used to record morbidity information if the child visits another clinic or is admitted. If the caregiver brings this book to the clinic visit, it can be used to inform the clinician. In addition, caregiver perceived morbidity is assessed (when possible) with phone call follow-up over the 12 week intervention period.

*Mortality* is the proportion of participant deaths recorded during the 12 week intervention period.

# Quality assurance

Study personnel will be trained in study procedures before they can participate in data collection or study conduct. The following list provides an overview of some of the procedures described in SOPs included in the training. Note that this is not an exhaustive list.

- Recruitment and referral
- Screening and inclusion
- Randomization and blinding
- Nutrition counselling
- Training caregivers in the correct storage and use of LNS & LNS distribution
- Training caregivers on stool collection at home
- Anthropometry
- Bioimpedance
- Sample (blood and stool) collection, labelling and storage
- Child development
- Clinical follow-up
- Phone follow-up
- WASH assessment
- Adverse event registration
- Discharge
- Data entry and data management
- LNS storage and disposal

# Data management

## Data entry

All participant data are collected on a paper case report form (CRF) and are double entered using Epidata software (<https://www.epidata.dk/>). The secure electronic data collection platform REDCap (Open Source Vanderbelt University) may be used for specific tasks such as participant registration and randomisation. However, these processes can be carried out without REDCap should an internet connection be unavailable. Data should be primarily entered into the CRF and not written down elsewhere unless stipulated in the SOP.. All study staff are trained extensively in how to fill in the sections of the CRF that are relevant to their role. Selected senior staff members are responsible for ensuring that data entry is complete.

## Coding

Data integrity is enforced with inbuilt value checks, data ranges and consistency checks in Epidata..

## Data security

If data is changed on a paper CRF, it is signed by the respective staff member in case a query arises. After a participant has been discharged from the study, both the informed consent form and hard copy of personal identifiers are kept in a secure and safe location away from the rest of the data. Hard copies of the CRFs are source data and are to be stored in numerical order according to the ID number in a secure but accessible place. All source data is kept securely on file for a minimum period of 5 years after completion of the study. The REDCap system is centralised at the University of Copenhagen on secure online servers which are monitored and backed up regularly.

## Data safety monitoring board

An independent data safety monitoring board (DSMB) has been established and all members have consented to participation on the board. The DSMB consists of four members:

- Chairman: [name], Paediatrician, World Health Organisation, Sierra Leone.
- Board Member: [name], PhD, Assistant Professor and MSc Nutrition for Global Health Programme Director, London School of Hygiene & Tropical Medicine, London, UK.
- Board Member: [name], PhD, bioethicist, senior lecturer at the College of Health Sciences and Chair of Biomedical Sciences Higher Degrees and Research Ethics Committee, Makerere University.
- Board Member: [name], BPharm, MSc and PhD in Medical Statistics. Honorary Assistant Professor at the Department of Medical Statistics, London School of Hygiene & Tropical Medicine, London, UK

The DSMB is a group independent of the study organisers who will monitor safety parameters. They will receive unblinded data including individual case fatality reports, SAEs and reasons for termination of participants. Based on this information, the DSMB will decide if the study can continue or if any actions are needed. There is one pre-defined stopping rule for the unlikely risk of high mortality: p< 0.01 after inclusion of 300 children. The safety monitoring board will have access to the randomization code and will not be blinded to the treatment of the children.

# Statistical methods

Primary, secondary, and tertiary endpoints are analysed by means of longitudinal data analysis accounting for the fact that repeated measurements are acquired per participant. Missing data will be handled by intention to treat analysis. A statistical analysis plan will be prepared before unblinding of the trial.

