## Discontinuation of participation in the study

Parents or caregivers are allowed to withdraw their child from the investigation at any time for whatever reason. The Investigator also has the right to discontinue participant investigations at any time if they deem that it is in the best interest of the participant or if non-compliance with the clinical protocol impacts on the scientific integrity of the clinical study. Possible reasons for premature withdrawal of a study participant include:

- Non-compliance with the clinical protocol impacting on the scientific integrity of the clinical study.
- If a child’s safety and well-being is compromised by further participation

In case of patient withdrawal, the CRF will be completed up to the point of patient withdrawal and all available data will be used in data evaluation/statistics. Withdrawn patients will not be replaced.

All participants requiring hospital attention will be referred for treatment. If a child is referred for hospital treatment, attempts will still be made to follow-up on the child wherever possible.

Early termination of a child from the study occurs due to the following reasons: the investigator sees fit to discontinue participation, the caregiver wishes to discharge, death and loss to follow-up.

If a child dies while enrolled in the study, the medical cause will be identified (if possible) by verbal autopsy, noted in the CRF and reported to the sponsor (as per the SAE reporting SOP).

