## Protocol deviations and violations

Protocol deviations are unplanned instances of non-compliance to the protocol. These are noted during the study, recorded and evaluated as major or minor before the blind of the study is broken. Any major protocol violations are reported to SOMREC within seven (7) calendar days of becoming aware of the event (in accordance with UNCST guidelines). All minor deviations from SOPs or the protocol will be reported in “Notes to file” and submitted with the annual progress reports to SOMREC, e.g. if a participating child does not provide a stool sample on time. Participants with major protocol deviations or violations are excluded from Per-Protocol-statistical analysis.

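### Intention to treat is named as the missing-data method, while withdrawal for non-compliance may end a child's measurements; the lost outcomes may bias the intention-to-treat estimates

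*Protocol*

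**What the plan says.** Section 25 (Statistical methods) says that endpoints are "analysed by means of longitudinal data analysis accounting for the fact that repeated measurements are acquired per participant". It then says "Missing data will be handled by intention to treat analysis", and that a statistical analysis plan will be written before unblinding.

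Section 28.2 (Discontinuation of participation in the study) allows the investigator to discontinue a child in the child's best interest or "if non-compliance with the clinical protocol impacts on the scientific integrity of the clinical study". Non-compliance appears again in the list of possible withdrawal reasons. After withdrawal, "the CRF will be completed up to the point of patient withdrawal and all available data will be used in data evaluation/statistics", and the child is not replaced. The section describes continued attempts at follow-up for children referred to hospital, but not for children discontinued for non-compliance.

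Section 28.6 (Protocol deviations and violations) says: "Participants with major protocol deviations or violations are excluded from Per-Protocol-statistical analysis".

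**The concern.** Two statements do not fit together. Section 25 relies on intention to treat to deal with missing data. That principle keeps every randomised child in the allocated arm but says nothing about the value of an outcome that was never recorded. Section 28.2 meanwhile allows some of those outcomes to go unrecorded for a reason that may be related to growth.

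The SAP can choose a model and a missing-data assumption, but it cannot recover a week-12 measurement that was not taken. The loss also serves no analytic purpose, because the per-protocol analysis already excludes children with major deviations.

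At stake is whether the estimates describe all randomised children. A longitudinal model that assumes data are missing at random treats a withdrawn child as continuing like comparable children who stayed. If non-compliance goes with poorer later growth, the arm mean is too high. Supplement non-compliance has no counterpart in the reference group, so the supplemented-versus-reference comparison is the most exposed.

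**Working it through.** **Inputs from section 18 (Sample size):** 0.35 SD, 5% significance (two-sided assumed), 80% power, 129 per group, 10% loss, 150 per group; 0.27 SD (4.9 mm) for 600 versus 150; SD of knee-heel length 18.1 mm.

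**Inputs not in the protocol, hence assumptions:** the share *w* of LNS children withdrawn early for non-compliance, and the amount *s* (in SD) by which they grow less than those who stay.

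1. *The plan's own figures reproduce.* n = 2 × (1.960 + 0.842)² / 0.35² = 128.1, so 129. Allowing 10% loss, 129 / 0.90 = 143.3, so 144; 150 covers this with some slack. With 540 versus 135 children left after 10% loss, the detectable difference is 2.802 × √(1/540 + 1/135) = 0.270 SD, and 0.27 × 18.1 = 4.9 mm.

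2. *Bias formula.* Let children who stay have mean *m* and withdrawn children *m* − *s*. The mean of all randomised LNS children is (1 − *w*)·*m* + *w*·(*m* − *s*) = *m* − *w*·*s*. An estimate that projects the withdrawn children from those who stayed gives *m*, so the LNS mean is overstated by *w*·*s*. This assumes no matching withdrawals in the reference group and no information from visits before withdrawal, so it is an upper-end figure for each pair of inputs.

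3. *Supplemented versus reference:*

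| *w* | *s* (SD) | Bias (SD) | Bias (mm) | Share of 0.27 SD |
| --- | --- | --- | --- | --- |
| 2% | 0.20 | 0.004 | 0.07 | 1.5% |
| 2% | 0.27 | 0.005 | 0.10 | 2% |
| 2% | 0.50 | 0.010 | 0.18 | 3.7% |
| 5% | 0.20 | 0.010 | 0.18 | 3.7% |
| 5% | 0.27 | 0.014 | 0.24 | 5% |
| 5% | 0.50 | 0.025 | 0.45 | 9.3% |
| 10% | 0.20 | 0.020 | 0.36 | 7.4% |
| 10% | 0.27 | 0.027 | 0.49 | 10% |
| 10% | 0.50 | 0.050 | 0.91 | 18.5% |

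   The 0.27 rows describe children who simply forgo a benefit equal to the detectable difference. The 0.50 rows need more: 0.5 × 18.1 = 9.05 mm, almost twice the 4.9 mm detectable difference, so these children would also need a worse prognosis.

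4. *MPI and WP contrasts.* Between two sets of products the bias is *w*₁*s*₁ − *w*₂*s*₂. It is zero when the share withdrawn and the growth forgone are alike, and arises only if withdrawals differ by product in one of these respects.

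**The case against.** Several points limit this concern, and most of them stand.

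- *The clause is discretionary and broad.* It covers any protocol non-compliance judged to affect scientific integrity, in any arm. The section on adherence (16) sets no withdrawal rule for poor supplement intake. A reader might infer that removal is one-sided against the reference group. The text does not say so: missed visits, for example, could count in arm E too. Only the supplement component is confined to arms A-D.
- *Withdrawn children are not dropped.* A reader might take section 28.2 as a per-protocol exclusion in disguise. It is not, because data collected before withdrawal are used, and anthropometry is scheduled at baseline and at weeks 2, 4, 8 and 12. Earlier visits reduce the bias but do not remove it if growth after withdrawal departs from what the model projects.
- *The exposed comparison is secondary.* Section 18 places 600 versus 150 in secondary analysis. The primary objective concerns MPI and WP, where the products are made to look and taste alike as far as possible and product allocation is blinded. Similar withdrawal across products would largely cancel.
- *The model and sensitivity analyses belong in the SAP.* Agreed; their absence from the protocol is not a fault. The fault in section 25 is that the one sentence it does give assigns the task to a principle that cannot perform it.

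Two things remain: the wording of section 25, and the ending of measurement in section 28.2. The objections answer neither.

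**Conclusion.** The point holds as a risk of bias, not as a demonstrated bias. Section 25 names a method that does not handle missing outcomes, and section 28.2 permits avoidable loss of outcomes that the SAP cannot restore.

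The size cannot be fixed from the protocol. Under the assumed 2-10% withdrawal and 0.2-0.5 SD deficit, the bias in the supplemented-versus-reference comparison is 0.004-0.05 SD before crediting earlier visits, about 1.5-19% of the 0.27 SD detectable difference. If the children forgo only a 0.27 SD benefit, it is 0.005-0.027 SD (2-10%). The top of the wider range rests on inputs that the protocol does not support and should not be read as an expected value. For the MPI and WP contrasts no figure can be given, and there is a bias only if withdrawals differ by product.

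A reader might also infer that such withdrawals threaten power. They draw on the same loss allowance as other losses, but 150 per group exceeds the 144 needed at 10% loss, so this is minor.

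**What to change.** **Section 28.2.** State that non-compliance does not end outcome measurement; that children discontinued for it are still invited to the scheduled measurements through week 12 unless the caregiver withdraws consent; and that non-compliance is handled only in the per-protocol analysis (section 28.6). Leave safety-based discontinuation as it is.

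**Section 25.** Replace the missing-data sentence with: *All randomised children are analysed as allocated, using all available visits in the longitudinal model; the missing-data assumption and sensitivity analyses are specified in the SAP.*

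**Cost.** A protocol wording change and some extra follow-up visits or tracing. The home visits already planned may help with tracing, but the protocol does not say that length or knee-heel length is measured there, so the measurements themselves may need clinic attendance. The change helps only children still in follow-up when it takes effect.
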